#### **10.3.4 Safety Evaluation**

Adverse events and serious adverse events will be coded using the Medical Dictionary for Regulatory Activities (MedDRA), and summarized by system organ class (SOC) and preferred term (PT). AEs will be summarized by solicited and unsolicited AEs as well. The treatment emergent adverse events (TEAEs) will be analyzed here. AEs occurring before vaccination will be listed.

All TEAEs, vaccine-related TEAEs, vaccine-unrelated TEAEs, Grade $\geq$ 3 TEAEs and vaccine-related Grade $\geq$ 3 TEAEs will be summarized by group. The frequency, subjects and percentage in each group will be reported. Fisher exact test will be used to compare the difference between the groups. The strat time and severity of TEAEs will be summarized. The vaccine-related TEAEs and vaccine-unrelated TEAEs will be listed.

All TESAE, vaccine-related TESAEs and vaccine-unrelated TESAEs will be summarized by group. The frequency, subjects and percentage in each group will be reported. Fisher exact test will be used to compare the difference between the groups. All TESAEs will be listed.

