**Safety endpoint:**

The incidence and severity of any adverse reactions/events within 30 minutes after vaccination;

The incidence and severity of solicited adverse reactions/events within 0-7 days after vaccination;

The incidence and severity of unsolicited adverse reactions/events within 8-30 days after vaccination;

The incidence of SAE and AESI observed after vaccination and up to 6 months after full course of immunization.

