#### **3.2. Secondary Objectives**

To evaluate the safety of recombinant COVID-19 vaccine (CHO cells) and inactivated COVID-19 vaccine (Vero cells) 28 days after sequential vaccination of one dose in population  $\geq 18$  years of age.

To evaluate the optimal immunization schedule of sequential vaccination of recombinant COVID-19 vaccine (CHO cells) in population  $\geq 18$  years of age.

To evaluate the immune persistence of sequential vaccination of recombinant COVID-19 vaccine (CHO cells) and inactivated COVID-19 vaccine (Vero cells) in population  $\geq 18$  years of

age.

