#### **4.3.2 Safety Endpoints:**

The incidence of any adverse reactions/events observed within 30 minutes after vaccination;

The incidence of adverse reactions/events observed within 0 ~ 7 days and 8 ~ 30 days after vaccination.

The incidence of SAEs observed up to 6 months after vaccination and full immunization.

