### **7.2.2 Safety Visit Procedure (Telephone Follow-up)**

Telephone follow-ups should be performed and evaluated according to the following procedures:

- ✓ Telephone follow-up subjects confirms that they have completed the diary card as required (until Visit 4 ).
- ✓ Evaluate whether the subjects are contraceptive and adhere to the lifestyle that meets the study requirements, evaluation the subjects' willingness and ability to conform to the study requirements.
- ✓ Evaluate and record any adverse events since the previous visit.

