## **7.3 Safety Observation and Follow-up**

### **7.3.1 Safety Observation**

(1) Observe the site for 30 minutes after vaccination to collect local and systemic adverse events.

(2) Telephone follow-up once in 6-24 hours after vaccination, within 1-3 days and 4-7 days respectively, the subjects were followed-up by telephone and guided to observe the adverse events

correctly and fill in the diary card.

(3) On the 14th day (Visit 4), the investigator reviews the filling of the diary card during this period and re-collect the diary card.

(4) On the 8th -30th day after vaccination, the investigator uses telephone follow-up once a week, combined with active report of the subjects to monitor the safety.

(5) When it is known that the subject has adverse reactions/events of Grade 3 or above, a face-to-face visit should take place within 24 hours.

(6) SAEs and AESIs are observed from the first dose to 6 months after the full course of vaccination by means of monthly telephone follow-up and self-reports from the subjects.

Note: Subjects should report respiratory tract infection symptoms such as fever and cough. Investigators should make comprehensive judgments, carefully identify whether it is common solicitation symptoms after vaccination or infection caused by other reasons, and closely observe the disease progress. Once the disease worsens, report it to the person in charge of the site quickly, and start the green treatment channel quickly to ensure that the subjects get timely diagnosis and treatment.

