| Observation at site after vaccination                     | ✓                                                                                       |                                                                                         |                                                                                           |                                                                                            |                                                                                            |                                                                                                    |                                                                                                    |                                                                                                    |                                                                                                     |
| Telephone follow-up after vaccination                                 | ✓                                                                                       | ✓                                                                                       | ✓                                                                                         |                                                                                            |                                                                                            | Once per month within D28-6M                                                                       |                                                                                                    |                                                                                                    |                                                                                                     |

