| Concomitant Medication                                                | ✓                                                                                       | ✓                                                                                       | ✓                                                                                         | ✓                                                                                          | ✓                                                                                          | ✓                                                                                                  | ✓                                                                                                  |                                                                                                    |                                                                                                     |
| Adverse events                                                        | ✓                                                                                       | ✓                                                                                       | ✓                                                                                         | ✓                                                                                          | ✓                                                                                          | ✓                                                                                                  | ✓                                                                                                  |                                                                                                    |                                                                                                     |

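### The protocol contradicts itself on how long non-serious adverse events are collected (day 30 or month 6), and the TEAE tests in 10.3.4 are not tied to the day 0-30 endpoints

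*Protocol*

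**What the plan says.** **Texts that end at day 30.** Section 4.3.2 defines the endpoint as "The incidence of adverse reactions/events observed within 0 ~ 7 days and 8 ~ 30 days after vaccination". The Synopsis has "The incidence and severity of unsolicited adverse reactions/events within 8-30 days after vaccination". Table 1 and 4.5.1 use the same two windows.

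**Follow-up to month 6, SAEs and AESIs only.** Section 7.3.1(6): "SAEs and AESIs are observed from the first dose to 6 months after the full course of vaccination by means of monthly telephone follow-up".

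**Texts that point to all adverse events up to month 6.** The "Adverse events" row of Table 4 is ticked at every visit from V1 to V7, so it includes V6 (3 months) and V7 (6 months). SAE has its own row with the same ticks. Table 4 schedules telephone calls "Once per month within D28-6M", and the list of tasks for telephone contacts in 7.2.2 includes "Evaluate and record any adverse events since the previous visit", with no end date and no restriction to serious events.

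**The analysis.** Section 10.3.4: "The treatment emergent adverse events (TEAEs) will be analyzed here. AEs occurring before vaccination will be listed". It then summarises all TEAEs, vaccine-related and unrelated TEAEs, and Grade 3 or higher TEAEs by group, with Fisher's exact test between groups. Vaccination is the only time boundary.

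**The objective.** Section 3.2: "To evaluate the safety of recombinant COVID-19 vaccine (CHO cells) and inactivated COVID-19 vaccine (Vero cells) 28 days after sequential vaccination of one dose". The Synopsis gives the same 28 days.

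**The concern.** A site that follows Table 4 and 7.2.2 will record every adverse event up to month 6. A site that follows 7.3.1(6) will record only SAEs and AESIs after day 30. Both would be following the protocol. If practice differs between centres, an analysis plan cannot afterwards recover events that some centres never recorded.

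Section 10.3.4 does not resolve this. Taken literally, every post-vaccination event in the database is a TEAE and enters the between-group tests. If non-serious events from after day 30 are in the database, the tables describe a 6-month risk, based partly on monthly recall, that no endpoint defines. Late illness unrelated to the vaccine would be expected in both arms at similar rates, which would pull the comparison towards no difference. In a safety comparison that direction matters, because it can hide a true excess.

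**Working it through.** **1. No safety figure to reproduce.** The protocol states no adverse-event rate and no power for safety. Its only computed figures are the immunogenicity sample sizes in 10.1 (208 and 250 per arm). They recompute to 207 and 249, and this point does not touch them.

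**2. The passages side by side.**

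| Place | Non-serious events collected or assessed until |
|---|---|
| 3.2 and Synopsis safety objective | day 28 |
| 4.3.2, Synopsis endpoints, Table 1, 4.5.1 | day 30 |
| 7.3.1(6) | only SAEs and AESIs named for follow-up to month 6 |
| Table 4, adverse-event row | month 6 (V7) |
| 7.2.2 with the Table 4 call schedule | month 6, all events |
| 10.3.4 | no last day |

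The conflict that matters is between the day-30 texts with 7.3.1(6), and Table 4 with 7.2.2. The gap between 28 and 30 days is 2 of the 23 days in the day 8-30 window (2/23 = 8.7%), and no planned analysis cuts at day 28.

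**3. Direction of the effect, if late events are pooled.** Let pT and pC be the day 0-30 risks in the two arms, and b the risk of a late background event, equal in both arms and independent of early events. The risk to month 6 in an arm is

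q = 1 - (1 - p)(1 - b).

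Hence qT - qC = (pT - pC)(1 - b). The risk difference shrinks by the factor (1 - b), and the risk ratio moves towards 1. This part is algebra and needs no assumed rate.

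**4. Illustration of size.** From the protocol: 900 per arm planned (10.1) and Fisher's exact test (10.3.4). Assumed, because the protocol does not give them: the risks p, the background b, and a two-sided 5% level. Example with pT = 20%, pC = 15%, b = 10%: qT = 1 - 0.80 × 0.90 = 28.0%, qC = 1 - 0.85 × 0.90 = 23.5%, difference 4.5 points = 5.0 × 0.90.

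Exact Fisher power by full enumeration for 20% vs 15%:

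| b | Risks (%) | Difference (points) | Risk ratio | Power |
|---|---|---|---|---|
| 0 (day 30 window) | 20.0 / 15.0 | 5.00 | 1.33 | 78% |
| 5% | 24.0 / 19.25 | 4.75 | 1.25 | 67% |
| 10% | 28.0 / 23.5 | 4.50 | 1.19 | 57% |
| 20% | 36.0 / 32.0 | 4.00 | 1.13 | 41% |
| 30% | 44.0 / 40.5 | 3.50 | 1.09 | 31% |

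Over the same values of b, power goes from 80% to 73%, 66%, 52% and 41% for assumed risks of 30% vs 24%, and from 87% to 66%, 50%, 32% and 22% for 10% vs 6%. The relative loss is larger where the early risk is lower.

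The Grade 3 or higher comparison follows the same formula with its own b. That b should be smaller, and it is not sized here.

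**The case against.** The strongest reply is that the day-30 window is stated many times, that 10.3.4 itself separates solicited from unsolicited events (which the Synopsis ties to days 0-7 and 8-30), and that the last day of a treatment-emergent period is routine content of a statistical analysis plan. On that view the missing end day alone is no defect. This is right: the point rests on the contradiction over collection, not on the silence in 10.3.4.

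Second, the Table 4 ticks have an innocent reading. Under 4.5.4 an AESI may be non-serious and is followed for 6 months, and Table 4 has no AESI row. Under 7.3.2 a persisting reaction is recorded until it resolves. The ticks at V6 and V7 may mean no more than that. This is possible, but it does not remove the conflict with 7.2.2, which asks for any event and is paired with monthly calls to month 6.

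Third, section 9 locks and unblinds the database for the safety evaluation after at least one month of safety follow-up. That fits a one-month main analysis, but it is a minimum and not a cut-off.

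A reader might infer that late events will dilute the arm comparison, with a known loss of power. The documents do not support that. Dilution needs late non-serious events to be both collected and pooled, and every rate behind the power figures is assumed. Nor would a true difference in reactogenicity be lost generally: solicited day 0-7 events are summarised separately and unaffected, and vaccine-related TEAEs are affected less. A reader might also treat the 28-day objective as an equally serious third window. It is a small mismatch of wording.

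**Conclusion.** The contradiction is real and stands in the current text. Non-serious adverse events end at day 30 under the endpoints, Table 1 and 4.5.1, with only SAEs and AESIs named for follow-up to month 6 in 7.3.1(6), but run to month 6 under Table 4 and 7.2.2. Because the TEAE tests have no last day, events from outside the endpoint windows could enter them.

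The consequence is conditional. If late events are pooled and their background risk b is equal in the arms and independent of early events, the risk difference shrinks by the factor (1-b). How large b would be cannot be told from the protocol, so the power figures are illustrations and not estimates. Safety is a secondary objective without a hypothesis or power claim, and neither the primary non-inferiority conclusions nor the sample size depend on this. It should be corrected because collection that differs between sites cannot be repaired later.

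**What to change.** - Reconcile Table 4 (adverse-event ticks at V6 and V7), 7.2.2 and 7.3.1(6) to one collection period for non-serious events. If the V6 and V7 ticks are meant for AESIs and follow-up of ongoing events, say so in a footnote, and limit 7.2.2 to match.
- In 10.3.4, tie the between-group TEAE tests to the endpoint windows: 30 minutes, days 0-7 and days 8-30. Report SAEs and AESIs from day 31 to month 6 separately.
- Minor: align the 28 days in the safety objective (3.2 and Synopsis) with the 30-day endpoint.

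Cost: an amendment of wording in 3.2, the Synopsis, Table 4, 7.2.2, 7.3.1 and 10.3.4. No extra visits, data or subjects are needed.

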### **10. STATISTICAL CONSIDERATIONS**

#### **10.1 Sample Size Considerations**

Assume 4-fold rise rate after sequential vaccination achieve 85%, 208 subjects in each arm will be required to have 80% power to conclude non-inferiority with margin of -10% and one-sided significance level of 2.5% using Miettinen & Nurminen method.

Equal GMT after sequential immunization is assumed, and standard deviation of GMT after log10 transformation is considered to be 0.7. 250 subjects in each arm will be required to have 80% power to conclude non-inferiority with margin of 2/3 and one-sided significance level of 2.5%.

Considering about 15%~20% drop-out rate, 600 subjects in three sequential cohorts (1-3 months, 4-6 months and ≥6 months after 2 doses), and 1800 subjects (900 subjects in test and control groups respectively) in total are planned to enroll.

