#### **10.2 Analysis Set**

Full Analysis Set (FAS): It includes all randomized participants who follow ITT principle, receive 1 dose of vaccine, and have valid immunogenicity data before the first dose.

Per-Protocol Set (PPS): It includes all participants who do not violate the inclusion criteria/exclusion criteria, receive 1 dose of vaccine, and have both valid pre- and post-vaccination immunogenicity data. PPS will be defined for immunogenicity evaluations 14 and 28 days after sequential vaccination, respectively.

Immunogenicity Persistence Set (IPS): It include the participants who are collected

with blood samples at each time point for immunogenicity persistence evaluation and with valid antibody data. Define the IPS for immunogenicity for 3, 6, 9, 12, 18 and 24 months after sequential immunization respectively.

Safety Set (SS): It includes all participants who receive one dose of vaccination.

In immunogenicity analysis, the participant who takes the vaccine erroneously will be included as randomized, and the safety data will be analyzed as treated.

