### **10.3.3 Immunogenicity Analysis**

ANCOVA model will be employed to analyze post-vaccination GMT. In the model, log-transformed GMT after vaccination will be included as dependent variable, pre-vaccination GMT after log-transformation is the covariate and group assignment and sequential vaccination time (1-3 months, 4-6 months and  $\geq 6$  months after the sequential dose) are the fixed effect. The adjusted LSMean in each arm and difference between the two groups together with 95% confidence interval (CI) will be estimated from the model. After inverse log-transformation, the adjusted GMT after vaccination and GMT ratio together with 95% CI between treatment and control groups will be derived. If the lower bound of 95%CI is larger than 0.67, the non-inferiority result will be concluded.

The 4-fold rise, and the proportions of antibody titered  $\geq 1:16$ ,  $\geq 1:32$  and  $\geq 1:64$  after vaccination in both vaccine and placebo groups will be estimated. The corresponding 95% CIs will be derived from Clopper-Pearson method. The difference between the two groups and their 95% CIs will be estimated by CMH method including the stratification factor (sequential vaccination time). If the lower bound of 95%CI in 4-fold rise rate is larger

than -10%, the non-inferiority will be concluded.

The descriptive statistics, including geometric mean and corresponding 95% CI, are employed to summarize GMT and GMI after sequential dose. The t-tests after log transformation will be compared between the two groups.

The reverse cumulative distribution plot is to depict the pre- and post-vaccination antibody data in the vaccine and placebo groups.

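### For rare safety events the protocol's only between-arm inference is an unstratified Fisher p-value, which says little about excess risk; a stratified risk difference with 95% CI should be the main comparison

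*Protocol*

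**What the plan says.** Safety is a secondary objective in Protocol section 3.2: "To evaluate the safety of recombinant COVID-19 vaccine (CHO cells) and inactivated COVID-19 vaccine (Vero cells) 28 days after sequential vaccination". Section 4.3.2 lists among the endpoints "The incidence of SAEs observed up to 6 months after vaccination and full immunization", and the synopsis adds AESIs over the same period. The Safety Set covers everyone vaccinated (section 10.2), and section 10.1 plans 900 subjects per arm.

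Section 10.3.4 gives the analysis. For all, related, unrelated, Grade 3 or higher, and related Grade 3 or higher TEAEs, "The frequency, subjects and percentage in each group will be reported", followed by "Fisher exact test will be used to compare the difference between the groups". The same pair of statements is repeated for treatment-emergent SAEs. The section mentions no risk difference, risk ratio, confidence interval, stratification or significance level.

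Section 10.3.3 handles binary immunogenicity outcomes differently. It asks for Clopper-Pearson intervals per arm and a between-group difference with 95% CI by the CMH method, stratified by sequential vaccination time. That is the randomisation factor in section 4.6.1.

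**The concern.** A test of no difference gives one of two answers. If it is significant, something is flagged. If it is not, the reader learns only that the data did not exclude equality, not how large an excess risk they leave open. For common reactions the reported percentages and 900 subjects per arm make this tolerable. For SAEs, where only a handful of events per arm may occur, a non-significant result is likely whether or not the recombinant booster carries more risk. The comparison required by the protocol would then carry almost no information on the safety outcomes of greatest concern. The protocol already uses a more informative method for another set of proportions in the same trial.

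**Working it through.** **The plan's own figures.** The protocol states no power or precision for safety. Its sizing rests on immunogenicity, and those figures reproduce:
- 4-fold rise (85% in both arms, margin 10 points, one-sided 2.5%, 80% power). The score formula uses restricted proportions 0.787 and 0.887: n = [1.96·√(0.787·0.213 + 0.887·0.113) + 0.842·√(2·0.85·0.15)]² / 0.10² = 207, against 208 stated.
- GMT (SD 0.7, margin 0.176 on the log10 scale): n = 2·0.7²·(1.96 + 0.842)² / 0.176² = 249, against 250 stated.
- Drop-out: 250/0.85 = 295 and 250/0.80 = 313, so 300 per arm per cohort covers about 16.7% loss (1 − 250/300). Three cohorts give 900 per arm.

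**Inputs for the safety check.** 900 per arm and 1:1 allocation come from section 10.1, and the Fisher test from section 10.3.4. Two inputs are assumptions: a two-sided 5% level, and the control event rates, which are shown as a range.

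**Step 1: power for a true doubling.** Power = Σ Bin(x₁; 900, 2c)·Bin(x₂; 900, c), summed over all tables with Fisher p ≤ 0.05, where c is the control rate.

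| Control rate vs doubled rate | Expected events (control, recombinant) | Power | Missed |
|---|---|---|---|
| 0.2% vs 0.4% | 1.8, 3.6 | 4% | 96% |
| 0.5% vs 1% | 4.5, 9 | 16% | 84% |
| 1% vs 2% | 9, 18 | 34% | 66% |
| 1.5% vs 3% | 13.5, 27 | 52% | 48% |
| 2% vs 4% | 18, 36 | 66% | 34% |
| 3% vs 6% | 27, 54 | 85% | 15% |
| 5% vs 10% | 45, 90 | 98% | 2% |

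Power crosses one half at a control rate of about 1.5%. Part of the loss at low rates is the conservatism of the Fisher test. With equal true rates of 0.2%, 0.5% and 1%, its actual two-sided size is 0.4%, 2.0% and 2.8%, not 5%.

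**Step 2: what the reader would see.** The Miettinen-Nurminen limits are the values δ that solve (p̂₁ − p̂₂ − δ)² / {[p̃₁(1−p̃₁)/n₁ + p̃₂(1−p̃₂)/n₂]·N/(N−1)} = 3.84. Here p̃ are the proportions restricted to differ by δ, and N = n₁ + n₂. These illustrations are unstratified.

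| Events, recombinant vs inactivated (900 each) | Fisher p | Risk difference (95% CI) | 95% CI for the risk ratio |
|---|---|---|---|
| 10 vs 5 | 0.30 | +0.56% (−0.32% to +1.54%) | 0.72 to 5.57 |
| 18 vs 9 | 0.12 | +1.00% (−0.13% to +2.24%) | 0.92 to 4.35 |
| 30 vs 15 | 0.033 | +1.67% (+0.23% to +3.21%) | 1.09 to 3.66 |

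An observed exact doubling first reaches p ≤ 0.05 at 28 versus 14 events. With 10 versus 5, the p-value of 0.30 says only that equality is not rejected. The interval shows that an excess of up to about 15 per 1,000, or a more than five-fold risk, remains compatible with the data.

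**The case against.** The strongest reply is that this is ordinary SAP detail. Only immunogenicity carries hypotheses and margins (section 4.4). Safety is secondary, and nothing in section 10.3.4 is false or forbids an interval. An SAP may well add intervals, so their absence from the protocol would not be a finding by itself. The point stands because the protocol does not stay silent: it selects a method for safety at the same level of detail at which section 10.3.3 selects a better one for proportions.

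A second reply is that an interval does not create power: with 10 versus 5 events it also includes zero. That is true. Its value is that it shows the remaining uncertainty.

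A reader might also infer several stronger things that the protocol does not support:
- **That safety is judged on p > 0.05 alone.** No decision rule is attached to the Fisher test. Percentages are reported per group, so a crude difference can be read off. Listings are planned, and the suspension criteria in section 7.6 act independently of any p-value.
- **That a doubling of severe reactions would usually be missed.** The protocol gives no Grade 3 or higher rate, and above about 1.5% in the control arm the reverse holds.
- **That the unstratified test is invalid.** With 1:1 allocation in blocks stratified by vaccination time it is valid, at most somewhat conservative. Stratifying is a matter of consistency with section 10.3.3.
- **That a safety margin is missing.** None is needed for a secondary objective without a hypothesis.
- **That power should be judged at 300 per arm.** Section 10.4 plans cohort analyses for immunogenicity only.

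**Conclusion.** The point holds for rare events. Section 10.3.4 makes an unstratified Fisher test the only between-arm safety inference beside counts and percentages. For events such as SAEs at an assumed control rate of 0.2% to 1%, a true doubling at 900 per arm would be non-significant in about 96% to 66% of trials, so the p-value alone says little about excess risk. This rests on a two-sided 5% level and on event rates that the protocol does not state. For events above about 1.5% in the control arm, a doubling is more likely to be detected than missed. This is a weak choice of method rather than an error or a contradiction, and it is worth changing because the better method is already in the protocol.

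**What to change.** In section 10.3.4, replace the statements on the Fisher test with text such as:

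*The main between-group safety comparison is the risk difference (recombinant minus inactivated) with its 95% CI, stratified by sequential vaccination time and calculated with the stratified Miettinen-Nurminen method. It is reported for any TEAE, vaccine-related TEAE, Grade 3 or higher TEAE, vaccine-related Grade 3 or higher TEAE, TESAE and AESI. Fisher exact p-values are descriptive flags only; a non-significant p-value is not evidence of similar safety.*

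The score-type interval is suggested because it remains usable with sparse or zero counts. No margin has to be set.

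The cost is a wording change and one extra column in the safety tables, with no new data or subjects. The one downside for the sponsor is that the statement on rare events will look less favourable, because the excess risk that cannot be excluded is shown.
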